## Trial design

The present study employs a naturalistic parallel groups design, integrating a regression discontinuity statistical approach for quasi-randomisation with a classical longitudinal design. The resulting pattern of evidence will indicate the sustainability, cost-effectiveness and effectiveness of the programme while we ensure that all study participants receive evidence-based treatment.

Assessments include an in-person baseline screening, monthly online or assisted self-assessments (hereafter: well-being monitor), and an in-person follow-up at 6–9 months post-baseline. Given the central role of the peer counsellors in the programme, we will assess their training and supervision in terms of acceptability, efficiency and motivations, through focus group discussions and survey-based evaluations. These evaluations will take place before the counsellors begin their active work and after they have completed a substantial number of NAT steps (screenings, referrals, checklist intakes, lifeline sessions and narrative event-telling sessions).

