## Interventions

### Explanation for the choice of comparators

In this naturalistic study, the following potential comparators to NAT (treatment condition) evolve: (1) NAT clients awaiting treatment; (2) clients with clinically relevant symptoms who are either (2a) waiting for psychotherapy or (2b) receiving psychotherapy; (3) clients without symptoms waiting for follow-up; and (4) clients before vs. after NAT (individual trajectories of symptom development, Table 1).

**Table 1 Tab1:** Constellation of comparators

Treatment condition	Control condition	Limitation	Mitigation
[1] NAT	Awaiting NAT (RHS 13–36)	Reduced follow-up time points for those who wait for treatment; unknown N	-
[2] NAT	[2a] PT waiting [2b] PT receiving	Clients might still wait but may have started, or already finished PT; higher symptoms of the control group at baseline	Statistical control for the number of treatment sessions, use of the RDD
[3] NAT	Watchful waiting (RHS < 13)	Lower symptoms of the control group at baseline, low symptom levels generally	Evaluate number of clients who present with improving vs. deteriorating symptoms rather than
[4] After NAT	Before NAT	Within subject comparison; potential confounding factors	-

Note: RHS-15 = 15 item Refugee Health Screener with a sum score indicating symptom severity; PT = Psychotherapeutic sessions provided by a licensed Psychotherapist. Threshold to clinical relevance is suggested for ≥37. Watchful waiting is indicated for clients with ≤12 points

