### Implementation

To assign participants according to the RDD principles, we will use the RHS-15 (items 1–13) as eligibility criteria with two critical thresholds at 13 and 36 (see Fig. 4) as foreseen in the stepped-care model of the *NAT counselling intervention*. The RDD then assumes that the allocation to the conditions is nearly random within the determined bandwidth (RHS sum scores just above or below the cutoffs) and potential factors that would manipulate treatment effect vary randomly across participants in both groups. The *fuzzy* versus the *sharp* design version takes into account real-world implementation settings recognizing that participants with RHS scores in the yellow range need to be assigned to the red group, for instance, in cases of suicidal ideation or other negative psychological developments that requires treatment by clinical psychologist.

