Generalised linear mixed models (GLMM) with subgroups defined by the RDD will be used in addition and allow for integration of multiple follow-ups, if robust (*N*_min_ is sufficient to detect a small to moderate effect). Thus, to test the efficacy of NAT in comparison to our controls in regards to primary and secondary outcomes, we plan to use separate generalised linear mixed models (GLMMs) in R. To account for non-independence of measurements, we will include individuals as a random part of the models. To account for repeated measures, we will control the within-group variance for the effect of time, i.e. baseline and 3 and 6-month follow-ups, according to A Field, Z Field and J Miles [179]. To estimate the significance of the fixed terms, we plan to fit the models using maximum likelihood (ML), and compare models with and without each fixed term using likelihood-ratio tests [180]. In cases where the interaction term is significant, we will use post hoc Tukey tests using the R package emmeans [181] to assess which contrasts differ significantly. To correct for multiple comparisons controlling the false discovery rate, we will further adjust P-values accordingly [182].

Additionally, effect sizes will be estimated by calculating Cohen’s d [183] for within and between group differences following W Lenhard and A Lenhard [184]. Clinically significant change will be calculated using the reliable change index, following NS Jacobson, LJ Roberts, SB Berns and JB McGlinchey [185].

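### For RHS, the additional GLMM takes the group-forming baseline score as its first outcome value, so regression to the mean alone creates an apparent effect against the psychotherapy and watchful-waiting comparators

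*Protocol article*

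**What the plan says.** All references are to the Protocol article. Under Implementation (allocation), "we will use the RHS-15 (items 1–13) as eligibility criteria with two critical thresholds at 13 and 36". Intervention description gives the bands: green up to 12, yellow 13–36, red 37 and above. The Abstract names RHS-15 as the primary outcome.

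Statistical methods for primary and secondary outcomes states that "Generalised linear mixed models (GLMM) with subgroups defined by the RDD will be used in addition", subject to sufficient numbers, for both primary and secondary outcomes. Individuals are a random effect, and on the repeated measures the text says "we will control the within-group variance for the effect of time, i.e. baseline and 3 and 6-month follow-ups". Fixed terms are tested by likelihood ratio. Post hoc contrasts follow "In cases where the interaction term is significant". The interaction is not named; group by time is the natural reading. Baseline RHS is not named as a covariate in this model. The preceding paragraph promises only adjusted analyses for unspecified confounders.

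Table 1 lists the comparators. Awaiting NAT (comparator 1) shares the 13–36 band with NAT. The psychotherapy comparator (2) is acknowledged to have higher baseline symptoms, and watchful waiting (3) lower. For comparator 3 the mitigation reads "Evaluate number of clients who present with improving vs. deteriorating symptoms rather than", and the cell ends there.

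**The concern.** A group chosen because its measured score was low will on average score higher when measured again, and a group chosen because its score was high will score lower. This happens without treatment whenever the retest correlation is below 1. If the selecting score is also the time-0 outcome, the change from baseline differs between groups by construction, and a group-by-time term cannot separate that from a treatment effect.

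For comparators 2 and 3 this is the situation in the GLMM for RHS. The results are to be combined with the RDD estimate to judge effectiveness (hypothesis 3), so a valid analysis would be read alongside one that can show an effect where none exists. Counting improving and deteriorating clients for comparator 3 is open to the same drift. In addition, clients at 0–12 on a 0–52 scale have little room to improve.

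**Working it through.** The article's text gives no figure for this model to reproduce; its power curves are in a figure that is not shown. The check is therefore a simulation under no treatment effect and no time trend.

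**Inputs from the article.** RHS range 0–52; bands ≤12, 13–36 and ≥37; expected participation 30–50% of about 1,500, that is 1,500 × 0.3 = 450 to 1,500 × 0.5 = 750.

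**Assumptions (not in the article).** Population mean 20, SD 11, retest correlation r = 0.6–0.8, N = 600 (midpoint of 450 and 750), 70% followed (600 × 0.7 = 420), two-sided 5% level. Scores were drawn as bivariate normal, rounded and clipped to 0–52. Change scores were compared by a Welch t-test, a two-time-point simplification of the GLMM.

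**Approximate formula.** Spurious difference in change ≈ (1 − r) × gap in baseline means. The simulated baseline means are about 6.5 (green), 23.0 (yellow) and 41.2 (red). At r = 0.7:
- NAT versus green: 0.3 × (23.0 − 6.5) ≈ 5.0 points
- NAT versus red: 0.3 × (41.2 − 23.0) ≈ 5.5 points

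**Simulation, full groups.** At r = 0.7 the mean changes are green +4.2, yellow −0.9 and red −6.4. NAT therefore looks better than green by 4.2 + 0.9 = 5.1 points and worse than red by 6.4 − 0.9 = 5.5 points.

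| r | versus green: points, rejection | versus red: points, rejection |
|---|---|---|
| 0.6 | 6.7, about 100% | 7.5, about 98% |
| 0.7 | 5.1, about 100% | 5.5, about 92% |
| 0.8 | 3.4, about 100% | 3.7, about 80% |

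**Restricted to a band around the cutoff, r = 0.7.**
- ±8 points: rejection about 57% (green) and 22% (red)
- ±5 points: rejection about 19% (green) and 9% (red)

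Repeat runs moved the point differences by about 0.1 and the rejection rates by about 2 percentage points.

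**Closer to the planned model.** A repeated-measures version used baseline and two follow-ups with a random intercept, assuming mean 20 or 25, SD 12, r = 0.5–0.8 and N = 450 or 750.
- Versus green, full groups: 3.5–8.9 points, 98–100% rejection
- Versus red, full groups: 3.6–9.5 points, 88–100% rejection
- Either cutoff, ±3 points: 0.5–1.8 points, 5.5–12% rejection
- NAT versus awaiting NAT, both 13–36 and allocation unrelated to score: difference about 0, 4–7% rejection

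**Remedy.** With follow-up RHS as the outcome and baseline RHS as covariate with side-specific slopes, false rejection on full groups was about 4–6%. With a single common slope it was 3.6–6.7%, and the mean spurious difference stayed between −0.20 and +0.15 points.

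**The case against.** Several points on the other side stand.
- Comparator 1 is the waiting-list control named in the Abstract. It comes from the same score band as NAT and is not affected if waiting is unrelated to score.
- The GLMM is additional and conditional on numbers. The RDD regresses follow-up on baseline RHS on each side of the cutoff and does not have this flaw.
- The phrase "with subgroups defined by the RDD will be used in addition and allow for integration of multiple follow-ups" does not say whether the full bands or only a bandwidth near the cutoff are analysed. With a narrow bandwidth the bias becomes small.
- For secondary outcomes the baseline value is not the sorting score, so any bias arises only through correlation with RHS.
- The Limitations section already warns that randomisation within the control groups is compromised.

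These points narrow the problem without removing it. Neither control for session numbers nor the use of the RDD elsewhere, Table 1's mitigations for comparator 2, protects a model that keeps baseline RHS as an outcome.

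A reader might also infer that the 3- and 6-month time points do not exist, because Trial design gives "an in-person follow-up at 6–9 months post-baseline". The article does not support that: the well-being monitor is monthly and Table 3 lists RHS-15 as given both online and face to face, so values near months 3 and 6 are planned. What is left open is which assessment supplies the 6-month value and how interviews after month 6 enter.

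Nor can error percentages be put on the improver/deteriorator counts. Table 1 gives no threshold, and the only change criterion named in the statistical methods is the reliable change index.

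**Conclusion.** The point holds for RHS against comparators 2 and 3. As described, the GLMM would attribute regression to the mean to group membership, favouring NAT versus watchful waiting and disfavouring it versus psychotherapy. The existence of the bias requires only a retest correlation below 1. Its size rests on the assumed mean, SD and correlation, and on whether full groups or a bandwidth are used: near-certain false rejection against watchful waiting on full groups, but only modestly above 5% very close to the cutoff. The improver/deteriorator count for comparator 3 has the same weakness.

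It would go too far to conclude that every comparison of NAT, or the effectiveness assessment as a whole, is invalid. The RDD contrast remains sound on this point, and so does the comparison with clients awaiting NAT if waiting is unrelated to score.

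**What to change.** In the GLMM for RHS, use only post-baseline RHS values as the outcome and enter baseline RHS as a covariate with its own slope on each side of the cutoff. State whether the model uses full groups or a bandwidth. Treat the improver/deteriorator counts and before–after change as descriptive, and rely on the RDD contrast already planned at the lower cutoff for the comparison with watchful waiting. Optionally, replace the fixed 3- and 6-month levels by actual months since baseline, so that all monthly and 6–9-month RHS values contribute.

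The cost is a change of analysis wording and no extra data collection. The price is somewhat lower precision and reliance on the form chosen for the baseline slope, which the article's planned checks of functional form and bandwidth can be extended to cover.

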	The number of participants with subclinical symptom levels at baseline who do not require treatment after 6–9 months is higher in participants who received NAT than in the control group.	The number of participants with subclinical symptom levels at baseline who do not require treatment after 6–9 months is equal in participants who receive the adapted NET compared to the control group.	2b
Is NAT **effective** (symptom reduction)?	Symptom reduction in participants with subclinical symptom levels is stronger in participants receiving NAT than in the control group (see Table 1).	Symptom reduction in participants with subclinical symptom levels is the same in participants receiving NAT compared to the control group (see Table 1).	3
[4] Is the programme generally cost-**effective**?	The financial costs of the NAT counselling intervention are lower than those of other interventions.	The financial cost of the NAT counselling intervention is equal to or higher than other interventions.	4

[2a+b] Chi-squared tests will be used to compare the frequency of participants with subclinical symptom levels requiring more/less intensive treatment during the programme. Logistic regression analysis will be considered to estimate the odds of refugees with or without NAT requiring more/less intensive treatment (Table 4).

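### The mixed-model post hoc step (Tukey tests) compares symptom levels while hypothesis 3 is about symptom reduction, and its P-values are then adjusted a second time

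*Protocol article*

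**What the plan says.** Table 4 (ref. 3) gives the null hypothesis as "Symptom reduction in participants with subclinical symptom levels is the same in participants receiving NAT compared to the control group (see Table 1"). This is a statement about change.

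Item [3] of the statistical methods section answers it first with the regression discontinuity design (RDD). It then adds a second analysis: "Generalised linear mixed models (GLMM) with subgroups defined by the RDD will be used in addition". The time points are "i.e. baseline and 3 and 6-month follow-ups". For the fixed terms the plan will "compare models with and without each fixed term using likelihood-ratio tests". The post hoc step follows: "In cases where the interaction term is significant, we will use post hoc Tukey tests using the R package emmeans [181"]. Its stated purpose is "to assess which contrasts differ significantly". The next sentence reads: "To correct for multiple comparisons controlling the false discovery rate, we will further adjust P-values accordingly".

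Table 1 lists the comparators. For the psychotherapy control it names as a limitation "higher symptoms of the control group at baseline". For watchful waiting it names lower baseline symptoms. Clients awaiting NAT have the same RHS range as treated NAT clients (13–36). The article does not say how many of these groups enter one model.

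**The concern.** Tukey's procedure compares means in pairs. After a group-by-time interaction, its usual reading is a comparison of group-by-time marginal means, which asks whether two groups sit at the same level. Two of the three between-group comparators differ from NAT in level by design, because the groups are formed on baseline RHS. For them a significant difference at 6 months may restate the allocation rule and say nothing about who improved more. A reader of the results could take it as evidence for or against NAT.

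The preceding interaction test helps only if it concerns the same pair. An overall test across three or more groups can be significant because of any one of them, for example a watchful-waiting group with little room to change.

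Tukey P-values are also already corrected for all pairs in the family. Adjusting them further for the false discovery rate penalises the same comparisons twice. This hurts most for NAT versus awaiting NAT, the only between-group comparator without a baseline gap by design.

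**Working it through.** The article states no sample size, power or error rate for this step, so there is no figure to reproduce.

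**Inputs from the article:** three time points; thresholds 13 and 36; direction of the baseline gaps (Table 1). A two-sided test is stated for the RDD only.

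**Assumed:** alpha 0.05; between- and within-person SD 5 each; change 0, −3, −5 points at 0, 3 and 6 months; NAT baseline mean 24; 30, 50 or 100 per group; baseline gaps of 0 to 17 points. The simulations use a random-intercept model with 2,000 to 4,000 runs, and an interaction F test stands in for the likelihood-ratio test.

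**Step 1: level against change.** Take NAT 24 → 19 and psychotherapy 41 → 36. The difference in change is (−5) − (−5) = 0; the difference in level at 6 months is 19 − 36 = −17. With 50 per group, SE = √(2 × (25 + 25)/50) = 1.41, so z = 17/1.41 = 12.0 against a Tukey critical value of 3.10 (3 groups × 3 times = 9 cells). For a gap of 5, z = 3.54; for a gap of 2, z = 1.41.

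**Step 2: the planned sequence (interaction test, then Tukey) when NAT and control improve identically.**

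| Model | Baseline gap | False NAT–control difference |
|---|---|---|
| Two groups | 0 (awaiting NAT) | about 0.2% |
| Two groups | 2–5 | 0.5–4% |
| Two groups | 10–17 | 4–5% |
| Three groups, watchful waiting unchanged | 2 | 2% / 5% / 13% |
| same | 5 | 24% / 61% / 96% |
| same | 10–17 | 70–72% / 91–92% / about 99.8% |

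Triplets are for 30, 50 and 100 per group. In the three-group model the interaction is significant in about 71%, 92% and 99.8% of runs, because watchful waiting does not change. A difference-in-change contrast rejects in about 4–6% throughout.

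**Step 3: direction.** Let NAT go 24 → 19 and psychotherapy 41 → 31. NAT's reduction is 5 points smaller, yet its level is 31 − 19 = 12 points lower. Even in a two-group model the sequence declares NAT significantly lower in 68% to 99.8% of runs.

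**Step 4: power for NAT versus awaiting NAT.** Assume 150 versus 75 and a standardised difference of 0.4. SE = √(1/150 + 1/75) = 0.141, and 0.4/0.141 = 2.83.
- One planned contrast: Φ(2.83 − 1.96) = 81%.
- Tukey over 12 cells (4 groups × 3 times, critical value 3.27): Φ(2.83 − 3.27) = 33%.
- Tukey over 6 cells (2 groups × 3 times, critical value 2.85): Φ(2.83 − 2.85) = 49%.

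The Tukey figures are before any further adjustment.

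**Step 5: would a change contrast serve every comparator?** No. Groups selected on baseline RHS regress toward the population mean. With between-person SD 12 and within-person SD 6, reliability is 144/(144 + 36) = 0.80. For baseline means about 18 points apart, the spurious difference in change is about 0.20 × 18 = 3.6 points. In simulation (450 people, RHS bounded at 0–52, the protocol's thresholds, the same 3-point true change for all, population mean 22–23, between-person SD about 12, within-person SD 3 to 6), the contrast of NAT with the ≥37 group rejected in about 38% to 94% of runs; other settings fall somewhat outside this range on both sides. For a random split of the 13–36 group into NAT and awaiting NAT it rejected in about 5%.

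**The case against.** The strongest reply is that hypothesis 3 is tested before Tukey is reached: a significant group-by-time interaction is itself the evidence of unequal change. This stands. A reader might infer that the plan will declare NAT different from a control that improves identically, whatever the model. The article does not support that. In a two-group model the interaction test holds such findings to about 5% or less, and for awaiting NAT to about 0.2%.

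The article also says only contrasts, not cell means, and emmeans can apply Tukey within time points. Its mention of separate models may mean one per comparator or one per outcome. If only two groups are compared within a time point, Tukey adds no correction and the power loss in step 4 disappears. The false discovery rate step could be meant across outcomes. All of this is fair, and it makes the inflation conditional. It does not change what Tukey tests compare, nor the problem of direction, and the word 'further' does place the second adjustment after the first.

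Mixed models on subgroups close to a cutoff would have gaps of only a few points, where the false-difference rate can be small. The simulated SDs are also crude: scores confined to 0–12 cannot have a baseline SD above 6, while the assumed total SD is √50 = 7.1. The rates therefore illustrate the mechanism and do not predict this study.

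Which contrasts to code could be left to an analysis plan. Here, though, the article has fixed a named test, a condition for using it and a second adjustment, so this is a stated choice and not an omission.

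**Conclusion.** The point holds in a limited form. The named post hoc test compares levels, and hypothesis 3 concerns change. False positives are not inflated in a two-group model. They can be if baseline-unequal groups share one model: from 2% to about 99.8% across the assumed gaps and group sizes, and large only when the gap is about 5 points or more. The article does not say that such a model will be fitted. In any model with a baseline gap, the level contrast can carry the opposite sign to the difference in reduction. Adjusting Tukey P-values again corrects twice; under the assumptions of step 4, power for NAT versus awaiting NAT falls from 81% to between 33% and 49% before that second step.

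A reader might also infer that difference-in-change contrasts would be safe for every comparator. They would not, because selection on baseline RHS brings regression to the mean. The mixed model supplements the RDD and is used only if numbers allow, which limits the weight of the point. It should be corrected, but it does not undermine the RDD estimate.

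**What to change.** - Replace the Tukey step by one pre-specified difference-in-change contrast for NAT versus awaiting NAT, at a named time point, estimated from the mixed model whether or not the overall interaction is significant.
- Apply the false discovery rate adjustment once, to the unadjusted P-values of the planned contrasts.
- For the psychotherapy and watchful-waiting comparators, report level and change contrasts from the mixed model as descriptive only, and base inference on the RDD estimate.
- State which groups enter each model.

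The cost is a few sentences and a few lines of emmeans code, with no new data. The downside is that exploratory pairwise comparisons of cell means lose confirmatory status. The awaiting-NAT contrast also keeps the limits that Table 1 already lists for it: fewer follow-up points and an unknown number of clients.
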